## Abstract

**Background:**

Most diagnostic tests for acute uncomplicated urinary tract infections (UTIs) have been previously studied in so-called single-test evaluations. In practice, however, clinicians use more than one test in the diagnostic work-up. Since test results carry overlapping information, results from single-test studies may be confounded. The primary objective of the Amsterdam Cystitis/Urinary Tract Infection Study (ACUTIS) is to determine the (additional) diagnostic value of relevant tests from patient history and laboratory investigations, taking into account their mutual dependencies. Consequently, after suitable validation, an easy to use, multivariable diagnostic rule (clinical index) will be derived.

**Methods:**

Women who contact their GP with painful and/or frequent micturition undergo a series of possibly relevant tests, consisting of patient history questions and laboratory investigations. Using urine culture as the reference standard, two multivariable models (diagnostic indices) will be generated: a model which assumes that patients attend the GP surgery and a model based on telephone contact only. Models will be made more robust using the bootstrap. Discrimination will be visualized in high resolution histograms of the posterior UTI probabilities and summarized as 5^th^, 10^th^, 25^th ^50^th^, 75^th^, 90^th^, and 95^th ^centiles of these, Brier score and the area under the receiver operating characteristics curve (ROC) with 95% confidence intervals. Using the regression coefficients of the independent diagnostic indicators, a diagnostic rule will be derived, consisting of an efficient set of tests and their diagnostic values.

The course of the presenting complaints is studied using 7-day patient diaries. To learn more about the natural history of UTIs, patients will be offered the opportunity to postpone the use of antibiotics.

**Discussion:**

We expect that our diagnostic rule will allow efficient diagnosis of UTIs, necessitating the collection of diagnostic indicators with proven added value. GPs may use the rule (preferably after suitable validation) to estimate UTI probabilities for women with different combinations of test results. Finally, in a subcohort, an attempt is made to identify which indicators (including antibiotic treatment) are useful to prognosticate recovery from painful and/or frequent micturition.

## Background

### General background

An acute uncomplicated urinary tract infection (UTI, cystitis) is defined as an infection of the lower urinary tract (bladder) in an otherwise healthy, nonpregnant, adult woman without known anatomical or functional abnormalities of the urinary tract. [1-4] A U.S. study reported a 60% lifetime risk of physician-diagnosed UTI.[5]

The main symptoms suggesting a UTI are dysuria and urinary frequency, whereas vaginal irritation and discharge have been reported to reduce the probability of a UTI being present.[6] Besides a UTI, an important cause of dysuria and frequency is a *Chlamydia *urethritis. Other infectious diseases in the differential diagnosis of a UTI are other types of urethritis (e.g. gonorrhoea), vaginitis, interstitial cystitis and genital herpes. [6-8] Since a UTI differs from these diseases in its natural course and treatment, a correct diagnosis is essential.

Empirical treatment of symptomatic women has been reported to be cost-effective.[9,10] However, only half of symptomatic women are found to have a UTI if defined by ≥ 10^5 ^colony-forming units (CFU)/ml.[11,12] Moreover, bacterial resistance to commonly used antibiotics (e.g. trimethoprim and fluoroquinolones) is rising, suggesting the need for more evidence-based prescribing. [13-16] Better diagnosis of UTIs might prevent women from being unnecessarily treated with antibiotics and be even more cost-effective.

### Diagnostic work-up

Diagnosis of UTIs in general practice consists of various medical history questions and laboratory investigations, of which nitrite and leukocyte esterase (LE) dipstick tests, microscopic examination of urinary sediment, and dipslide are the ones most widely used.

Most diagnostic tests for UTIs have been studied before in single-test evaluations, implying that a test is compared to the urine culture, not taking into account the distribution of other test results in the population studied. [17-19] In practice, however, the diagnostic work-up is inherently multivariable, and test results are mutually dependent. [20-36] Therefore it cannot be generally expected that a test's sensitivity is invariant over different degrees of prior testing. For example, the sensitivity of the nitrite dipstick test will be affected by the information contained in the diagnostic profile resulting from prior test results.[37]

The primary objective of the Amsterdam Cystitis/Urinary Tract Infection Study (ACUTIS) is to determine the (additional) diagnostic value of relevant tests from patient history and laboratory investigations, taking into account their mutual dependencies. Next, an easy to use, multivariable diagnostic rule (clinical index) will be derived. After suitable (external) validation, GPs may use the (validated) rule to estimate UTI probabilities for women with different combinations of test results.

Little et al. and McIsaac et al. described similar work in a UK and a Canadian population, respectively.[38,39] However, different inclusion criteria were used (see further) and urine samples were transported as in routine practice before cultures were made, whereas in ACUTIS, to assure reliability of the cultures (= reference standard), urine samples are being refrigerated until being cultured. Furthermore, both earlier studies did not assess diagnostic values of the sediment and dipslide investigations.

Other similar studies.[40,41] were performed before the European Urinalysis Guidelines.[42] recommended a cut-off value of 10^3 ^cfu/ml for significant *Escherichia coli *bacteriuria and therefore only used the traditional cut-off value of 10^5 ^cfu/ml. Besides, they did not assess dipstick investigations and/or were not performed in a primary care setting.[41]

### Prognosis and natural history

Placebo arms of randomized controlled trials suggest that 25 to 50% of women presenting with a combination of UTI-symptoms and bacteriuria will have recovered in one week without using antibiotics. [43-45] Using data from ACUTIS, we will try to make a prognostic index. Using the prognostic index, a GP can estimate the 7-day course for women with different combinations of test results and decide which women are most likely to benefit from antibiotic treatment.

## Methods

### Setting

ACUTIS is performed in general practices and primary health care centers in Amsterdam and surroundings, which altogether comprise 20 practices of average size (total source population = 46,000 patients).

### Design

In a prospective cohort, each participating patient will be followed for 7 days. At baseline, potentially relevant signs and symptoms will be recorded and potentially relevant laboratory tests (dipstick, sediment and dipslide) will be performed, along with a urine culture as reference test. Details are described below.

### Study population

Eligible are female patients over 12 years of age, contacting their GP with painful and/or frequent micturition. The symptoms may have been present for a maximum of 7 days. Although not being adult and therefore not strictly meeting the definition of acute uncomplicated urinary tract infection, patients between the age of 12 and 18 are eligible, as their urogenital tract is expected to be anatomically similar to that of adult women.

Exclusion criteria are: pregnancy, lactation, signs of pyelonephritis, being immunocompromised (e.g. receiving radiotherapy or immunosuppressants, being HIV infected) with the exception of diabetes mellitus, having used antibiotics for another indication than UTI or having undergone a urological procedure in the past two weeks, and known anatomical or functional abnormalities of the urogenital tract.

To ensure a clinical domain in which the diagnostic index may be expected to perform as reported and to enhance generalizability in time and place, we use clearly formulated eligibility criteria. This differs from similar studies, in which patients were eligible when GPs "suspected" a UTI, based on their personal judgement.[38,39]

### Informed consent

A letter with information about the study is provided to all patients. Participating women must provide written informed consent prior to enrollment. For patients under the age of 18 written parental authorization is required.

### Sample size

When the events per variable (EPV) rule.[46,47] is applied on a number of 15 possible diagnostic indicators and taken into account that some indicators will have to be modeled as dummy variables, about 200 women with a UTI are needed for this study (although a more recent simulation study suggests that the traditional EPV figure may be an overestimate.[48], so that less patients may be needed for our study). Assuming that the probability of a UTI (if defined by ≥ 10^5 ^CFU/ml) in eligible women is approximately 50%.[11,12] (range 40–60%), between 333 and 500 women will have to be included in the study. According to a UTI incidence in The Netherlands of 68 per 1000 women per year.[49], 157 women per year are diagnosed with a UTI in a general practice of average size. Assuming that 80% of all eligible women will not take part in the study, 16–17 practices of average size that include patients for a period of 1 year are needed (500/(157 × (1-0.8)) = 16.03).

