### Dependent variable

The results of the urine culture will be used as the dependent variable. A cut-off value of 10^3 ^CFU/ml will be used to define a positive culture, as is recommended by the European Urinalysis Guidelines.[42] We will explore how sensitive the model is to the use of different cut-off values for defining a positive culture.[6,12,57-60]

Theoretically, false positive reference standard results may occur if women with asymptomatic bacteriuria are included in the study when they visit their GP with complaints similar to UTI symptoms but caused by a different disease (e.g. vaginitis). In the community, the prevalence of asymptomatic bacteriuria has been reported to be 1 to 5% in premenopausal, nonpregnant women, growing with increasing age to >10% in women over 70 years of age.[61]

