#### Variable selection

At the time of writing, a failsafe model selection strategy on which all statisticians and other experts in diagnostic and predictive modeling agree does not appear to exist. However, in his book 'Regression modeling strategies (2001)'[62], Harrell made some general proposals for researchers to tailor to the specific circumstances. We intend to use penalized logistic regression, and Tibshirani's *lasso *(least absolute shrinkage and selection operator)[63] in particular to combine the requirements of counteracting over-optimism (shrinkage of regression coefficients) while leaving the opportunity that some coefficients are set to zero, which serves the requirement of a parsimonious model. Bootstrapping will be used to estimate the penalization coefficient.[62] As a form of sensitivity analysis, we shall also explore bootstrapped stepwise regression[64,65] to see how well these approaches concur. We will avoid univariable preselection of predictors. The linearity assumption will be checked for all continuous predictors.

Discrimination of the model(s) will be visualized in high resolution histograms and summarized as 5^th^, 10^th^, 25^th ^50^th^, 75^th^, 90^th^, and 95^th ^centiles of these, Brier score and the area under the receiver operating characteristics curve (ROC) with 95% confidence intervals (overall discrimination).[66]

Using the regression coefficients of the independent diagnostic indicators, an easy to use, multivariable diagnostic rule (clinical index) will be derived, consisting of relevant tests and their diagnostic values.

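### The lower sample-size bound of 333 women is too low under the plan's own events-per-variable rule, and the prevalence behind the range belongs to a different culture cut-off from the modelled outcome

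*Protocol article*

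**What the plan says.** The Sample size section of the protocol article applies the events-per-variable rule. The rule "is applied on a number of 15 possible diagnostic indicators", with an allowance for dummy variables, and leads to the requirement that "about 200 women with a UTI are needed for this study". No number is required for women without a UTI.

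The total is then derived from a prevalence: "Assuming that the probability of a UTI (if defined by ≥ 10^5 ^CFU/ml) in eligible women is approximately 50" per cent, with a range of 40–60%. The result is that "between 333 and 500 women will have to be included in the study". The number of practices is calculated from the upper figure only: "500/(157 × (1-0.8)) = 16.03".

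Under Statistical analysis, the Dependent variable section sets a different threshold for the outcome: "A cut-off value of 10^3 ^CFU/ml will be used to define a positive culture". Other thresholds are left to a sensitivity exploration: "We will explore how sensitive the model is to the use of different cut-off values for defining a positive culture". The Variable selection section names the model: "We intend to use penalized logistic regression", with the lasso as the specific method.

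**The concern.** There are two separate problems.

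First, the calculation counts only one of the two outcome groups. Recoding culture-negative as the event gives the same logistic model with the signs reversed, so the amount of data needed cannot depend on which group is called the event. An events-per-variable target therefore applies to the smaller group. Dividing 200 by the prevalence makes 60% look like the most favourable case, although by symmetry it is as demanding as 40%.

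Second, the prevalence used for sizing is that of a UTI at 10^5 CFU/ml, but the models will be fitted to an outcome cut at 10^3. The Background section (Diagnostic work-up) presents the lower threshold as a deliberate difference from earlier studies. Nothing in the document gives a prevalence at 10^3 or explains why the 10^5 figure may stand in for it.

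At stake is whether the stated total supports the planned number of candidate tests. Too few women in the smaller group makes the coefficients and the choice of tests less stable, which is what the calculation was meant to guard against.

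**Working it through.** **Inputs, all from the protocol article**
- Required count: about 200 (Sample size).
- Prevalence p: central value 50%, range 40–60%, at 10^5 CFU/ml or more (Sample size).
- Outcome cut-off: 10^3 CFU/ml (Dependent variable).
- Recruitment: 157 women per practice per year, 80% non-participation (Sample size); 20 practices (Setting).
- Not given: the events-per-variable figure, the exact parameter count, and the prevalence at 10^3.

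**Step 1. Reproduce the stated range.** N = 200/p gives 200/0.60 = 333.3, 200/0.50 = 400 and 200/0.40 = 500. The stated limits of 333 and 500 are reproduced, so the division itself is correct.

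**Step 2. Count both groups at 333.** At p = 0.60 there are 333 × 0.60 ≈ 200 women with a UTI and 333 × 0.40 ≈ 133 without. The smaller group is 67 short of 200.

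**Step 3. Can any prevalence rescue 333?** The smaller group is largest at p = 0.50, where it is 333/2 = 166.5. So 333 cannot give 200 in both groups.

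**Step 4. Apply the rule to the smaller group.** N = 200/min(p, 1 − p):

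| p | N by 200/p | N by 200/min(p, 1 − p) |
|---|---|---|
| 40% | 500 | 500 |
| 50% | 400 | 400 |
| 60% | 333 | 500 |

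The range becomes 400–500. Only the lower limit moves.

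**Step 5. The cut-off.** Every culture of at least 10^5 is also at least 10^3, so prevalence at 10^3 is no lower than at 10^5. Its size is unknown, so the values below are assumptions:

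| Assumed p at 10^3 | Required N | Smaller group at N = 500 |
|---|---|---|
| 45% | 200/0.45 ≈ 444 (445 rounded up) | 225 |
| 50% | 400 | 250 |
| 60% | 500 | 200 |
| 65% | 200/0.35 = 571.4, so 572 | 175 |
| 70% | 200/0.30 = 666.7, so 667 | 150 |

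The total of 500 fails only above 60%.

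**Step 6. Recruitment.** The protocol's formula yields 157 × 0.2 = 31.4 women per practice in a year. For 572 women that is 572/31.4 ≈ 18.2 practices; for 667 it is 667/31.4 ≈ 21.2. The plan needs 16–17 practices and has 20.

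**The case against.** The strongest reply is that 333 drives nothing. The number of practices is computed from 500, and by the corrected formula 500 suffices for every prevalence from 40% to 60%. This stands, and it limits the harm. It does not make 333 an adequate total under the rule the section applies.

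A second reply is that the protocol itself says the traditional events-per-variable figure may be too high, and that lasso shrinkage with a bootstrapped penalty, plus a stepwise sensitivity check, protects against overfitting. This softens the consequence. But the remark concerns how many events each variable needs, not which group is counted, and the section still adopts 200. Shrinkage does not turn 133 into 200. So it would go too far to say that the models will be overfitted.

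Three stronger readings are tempting, and the document does not support them:
- A reader might infer that recruitment will stop at 333 women or at the 200th UTI. No such stopping rule is stated.
- A reader might infer that the lower cut-off necessarily leaves women without a UTI in short supply. The stated range starts at 40%. If prevalence at 10^5 were 40% and at 10^3 were 45% or 50%, the required total would fall from 500 to about 444 or to 400. The mismatch can ease the requirement as well as tighten it.
- A reader might infer exact events-per-variable ratios. Taking 200 to mean 20 parameters at 10 each is plausible, but the protocol states neither number.

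The planned exploration of other cut-offs does not answer the second problem. It concerns how the fitted model changes, not whether the total suits the main outcome.

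**Conclusion.** The point holds in two parts of unequal certainty.

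The lower bound of 333 is wrong as written. This rests only on the protocol's own target of about 200 and on the symmetry of the logistic model. The corrected range for 40–60% prevalence is 400–500, and the worst case of 500 is unchanged. It would overstate the matter to call the whole range wrong.

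The mismatch between the sizing prevalence (10^5) and the outcome (10^3) is a definite inconsistency, but its effect cannot be sized from the document. It threatens the total of 500 only if prevalence at 10^3 exceeds 60%. At an assumed 65% or 70%, 500 women would leave 175 or 150 culture-negative women against a target of 200. At 70%, the required total would also exceed what 20 practices yield in a year by the protocol's formula (20 × 31.4 = 628).

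**What to change.** In the Sample size section:

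1. State the target as about 200 women in the smaller of the culture-positive and culture-negative groups, at the 10^3 cut-off used for the dependent variable.
2. Replace the range with 400–500 women for a prevalence of 40–60%.
3. State the prevalence range assumed at 10^3, with its basis, and give the resulting smaller-group counts at a total of 500.
4. If that range goes above 60%, either raise the total and recheck the number of practices, or keep 500 and reduce the candidate parameters, dummies included, in proportion to the smaller group. At 65% that is 175/200 = 87.5% of the planned number, and at 70% it is 150/200 = 75%. If 200 stands for 20 parameters at 10 each (an assumption), these are 17 and 15.

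The first three changes are mainly rewording, at the price of a less favourable lower bound. The fourth has a real cost, in candidate parameters or in women, and arises only if prevalence at 10^3 exceeds 60%. Staying at 500 in that case is consistent with the rule only with the reduced parameter count.

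### The 157 UTI diagnoses per practice match a rate per 1000 women multiplied by a list of both sexes, so the 16-17 practices and one-year period do not follow from the protocol's stated inputs

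*Protocol article*

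**What the plan says.** The Sample size section of the protocol article first sets the target: "about 200 women with a UTI are needed for this study", and, with an assumed UTI prevalence of 40-60% in eligible women, "between 333 and 500 women will have to be included in the study".

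It then turns the upper target into a number of practices. The rate is introduced with "According to a UTI incidence in The Netherlands of 68 per 1000 women per year", and from it the section concludes that "157 women per year are diagnosed with a UTI in a general practice of average size". Participation enters through "Assuming that 80% of all eligible women will not take part in the study". The result is printed as "500/(157 × (1-0.8)) = 16.03" and read as 16-17 practices recruiting for one year.

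The size of an average practice comes from the Setting section, which describes the participating sites as "20 practices of average size (total source population = 46,000 patients". The text does not say that this population is women only. The Study population section admits only females over 12 years of age.

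**The concern.** The rate has women as its denominator, so it must be multiplied by the number of women on a practice list. The stated 157 seems instead to come from the full list. If so, the expected supply of participants per practice is too high by the inverse of the female share, roughly a factor of two, and both the number of practices and the one-year period rest on it.

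What is at stake is feasibility. If recruitment stops after the planned year, the cohort may hold fewer UTI events than the 200 judged necessary for about 15 candidate indicators, some of them coded as several dummy variables. The end-2009 date for submitting first results, given in the Discussion, would also be affected.

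**Working it through.** **Inputs from the protocol article.** Sample size section: incidence 0.068 per woman-year; 157 diagnoses per practice; 20% participation (1 − 0.8); 200 events; prevalence 40-60%. Setting section: 20 practices, 46,000 patients.

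**Assumption, not in the document.** Female share of the list 50%, with 48-55% as the range.

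**1. Reproduce the plan's figures.**
- Women to include: 200/0.6 = 333; 200/0.5 = 400; 200/0.4 = 500. These agree with the text.
- List per practice: 46,000/20 = 2,300 patients.
- Whole list times the rate: 2,300 × 0.068 = 156.4, essentially the stated 157.
- Denominator implied by 157: 157/0.068 = 2,309 women. With half the list female, that needs about 4,600 patients per practice, twice what the Setting section gives.
- Printed quotient: 500/(157 × 0.2) = 15.92, not 16.03. The printed value needs 156: 500/(156 × 0.2) = 16.03. The 0.7% difference is immaterial in itself.

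**2. Use women only, with the rate as labelled and the protocol's formula otherwise unchanged.**
- Women per practice: 2,300 × 0.50 = 1,150.
- Diagnoses per practice-year: 1,150 × 0.068 = 78.2.
- Participants per practice-year: 78.2 × 0.2 = 15.64.
- Practice-years for 500 women: 500/15.64 = 32.0.
- Yield in one year: 16 practices 250; 17 practices 266; 20 practices 313.
- Time with 20 practices: 500/312.8 = 1.60 years (about 19 months); 400/312.8 = 1.28 years (about 15 months).

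**3. Vary the female share.**

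| Female share | Diagnoses per practice-year | Practice-years for 500 | Women from 20 practices in a year |
|---|---|---|---|
| 48% | 75.1 | 33.3 | 300 |
| 50% | 78.2 | 32.0 | 313 |
| 52% | 81.3 | 30.7 | 325 |
| 55% | 86.0 | 29.1 | 344 |

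Twenty practices reach 333 in a year when diagnoses are 333/(20 × 0.2) = 83.25 per practice. That means 83.25/0.068 = 1,224 women, or 1,224/2,300 = 53% of the list.

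**4. Vary the ratio of eligible to diagnosed women, at 50% female.** The formula sets this ratio to 1 without saying so. Practices needed for 500 women in one year are 32.0 divided by the ratio:
- ratio 1.25: 25.6
- ratio 1.5: 21.3
- ratio 2: 16.0

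The 20 listed practices would reach 500 in a year at a ratio of 500/312.8 = 1.6.

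**The case against.** The strongest reply is that the formula sets unlike quantities against each other, and that this may offset the slip. The rate counts women diagnosed with a UTI, whereas the 333-500 target counts all eligible women with symptoms. The same section puts UTI prevalence among eligible women near 50%. If diagnosed UTIs are taken as true UTIs, 78.2 diagnoses imply about 156 eligible women per practice, and 200 events need only 200/(78.2 × 0.2) = 12.8 practices for a year.

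This stands as a possibility and limits the conclusion. It is not the protocol's argument. The formula applies the 80% non-participation, which is defined over eligible women, directly to the diagnosed count. The 50% is culture positivity at 10^5 CFU/ml among symptomatic women, not the fraction whom GPs diagnose, and the General background section itself raises empirical treatment and unnecessary antibiotics. The exclusions and the age limit reduce the eligible pool.

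Second, the label may be the error. The cited source is not available here. If its rate is per 1000 patients, the multiplication by 2,300 is right and the wording is wrong. A reader might infer that 157 must become 78; the document does not settle that.

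Third, the need may be smaller than 500. That is the worst case of the prevalence range, with 400 at its centre. The authors note that the events-per-variable rule may ask for too many, and the primary cut-off of 10^3 CFU/ml can only keep or raise the share of positive cultures. These points soften the consequence. However, the practice count was computed for 500, and 313 women would give 200 events only at a prevalence of about 64% (200/313), above the stated range for the 10^5 cut-off.

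Finally, 20 practices are listed against 16-17 required. That is a margin of 18-25% (20/17 to 20/16), which does not absorb a discrepancy of about twofold.

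**Conclusion.** The Sample size and Setting sections contradict each other as printed. A rate stated per 1000 women reproduces the 157 only when applied to all 2,300 patients. This follows from the document's own figures and needs no assumption.

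The size of the consequence does need assumptions: that the rate is per 1000 women as printed, that about half the list is female, and that diagnosed women stand in for eligible women as in the protocol's formula. On these, 500 women need about 32 practice-years (29-33 over a female share of 48-55%) rather than 16-17. In one year, 16-17 practices yield about 250-266 women and all 20 about 313 (300-344).

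A reader might infer that the study cannot recruit its sample, or that the 20 practices must miss even the lower target of 333. Neither is established. The first fails if eligible women sufficiently outnumber diagnosed women, and the gap closes at a ratio near 2. The second holds only below about 53% female, and only while that ratio is close to 1. The targets of 200 events and 333-500 women, and the planned models, are untouched; the defect lies in the practice count and recruitment time.

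**What to change.** Check the denominator of the cited incidence and correct whichever term is wrong.

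- **If it is per 1000 women:** restate the diagnoses per practice (about 78), the practice-years (about 32 for 500 women) and the recruitment period for the 20 practices (about 19 months for 500, about 15 for 400), all at 50% female. Write the female share into the formula.
- **If it is per 1000 patients:** correct the wording, and count only the women among the diagnoses, since only women are eligible.

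In either case, state the assumed ratio of eligible to diagnosed women as a term in the formula, even if it is 1, with a basis for it. Correct the printed quotient so that it agrees with its inputs (15.92 with 157; 16.03 needs 156).

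The cost is a few lines of corrected text and, if the shortfall is confirmed, a longer stated recruitment period, with the end-2009 submission date rechecked. Nothing in the data collection or analysis has to change.
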